#### Systematic training of local CHWs

Enhancing the capacity of local CHWs through systematic training is a key feature of the intervention model. Training of local CHWs in the intervention group will consist of an initial training on the intervention protocol, including education on the targeted CVD lifestyle risk factors and the medications being utilized, followed by refresher training about 1–3 months after the intervention begins. Only CHWs who pass the initial evaluation examination can take part in implementing the intervention. After the training, CHWs will be provided with a list of high-risk individuals screened out at baseline for them to contact and manage according to the protocol.

In Tibet, China, "village doctors" who are not physicians but have basic professional training and can prescribe medications will be chosen to be the CHWs to implement this management plan. In rural India, local women will be recruited and trained to be the study’s CHWs. Because the Indian CHWs have no prior medical experience, they will be partnered with licensed physicians from nearby primary health care centers who are responsible for the prescription duties based on the CHWs’ regular assessments of their assigned high-risk patients.

#### Electronic decision support

An electronic decision support (EDS) component will be incorporated in this study to assist the CHWs on the follow up and management of their high-risk patients during the one-year intervention period. The EDS system is a smartphone or tablet-based android application that will be developed and pilot tested based on the ‘2 + 2’ intervention model and consists of prompts regarding the patient’s medical history, new conditions, medication usage, current lifestyle habits, blood pressure, and the appropriateness for prescribing any of the target medications. The follow-up records entered into the device can be easily uploaded by CHWs to a central server to generate performance indicators and provide feedback to help improve the quality of care. In India, the EDS system has a desktop component for the use of physicians to prescribe drugs in the intervention arm.

#### Performance feedback

Tiered monetary payments based on key performance indicators will be given to CHWs on a recurring basis. Examples of key performance indicators include the number and percentage of high-risk individuals receiving regular follow-up, lifestyle advices, and medications.

#### Control

Villages in the control group will continue their usual practices without any of the above mentioned interventions. Usual practices will include any other government or project-initiated lifestyle, hypertension or cardiovascular management programs.

### Outcome evaluation

#### Baseline and post-intervention survey

The outcome evaluation for this study will be derived from data collected from the baseline survey and post-intervention follow-up survey of all eligible and consenting high-risk patients in the intervention and control villages. Both survey questionnaires will be identical, and include information on patient’s demographics, disease history, lifestyle behaviors, medication use, primary healthcare services utilization, hospitalizations, and medical care related expenses in the past year. Height, weight, waist circumference, and blood pressure will be measured at that time of the survey. Surveys in both countries will be conducted by trained personnel according to the same standardized operating procedures. The questionnaires used in China and India will be kept nearly identical except for a few variations to fit the cultural context and target the specific lifestyles of the two peoples in these countries such as different types of tobacco use (See Table 
1 for survey indicators).

**Table 1 Tab1:** **Indicators followed in baseline and follow-up survey**

Indicators	Measures	Methods
Behavioral	Tobacco	Questionnaire
	Alcohol*	
	Physical activity	
	Salt consumption	
Anthropometric	Height	Stadiometer
	Weight	Weighing machine
	Waist circumference	Measuring tape
	Blood pressure	Electronic BP monitor
Treatment history, Health services, Health care costs	Compliance	Questionnaire
	Awareness, Risk factor control	
	Service utilization	
	Treatment cost	

*: Not covered in Tibet, China site.

The primary outcome will be the net difference between the intervention and control groups in the pre- and post-intervention change in the proportion of high-risk individuals treated with anti-hypertensive medication, obtained through the two surveys described above. This process indicator is chosen for its close association with the intervention scheme, effect on lowering high blood pressure, and its excellent power.

A number of secondary outcomes will also be evaluated, including the net difference between the intervention and control groups in the pre- and post-intervention change in the proportion of high-risk individuals treated with aspirin, the net difference in mean blood pressure from baseline to follow-up in high-risk individuals between the intervention and control villages, as well as hypertension awareness, treatment, and control rates. Awareness of modifiable lifestyle risk behaviors will also be assessed, specifically on the proportion of high-risk individuals aware of the harms of smoking and consumption of a high salt diet. Finally, the proportion of high-risk individuals receiving five or more follow-up visits from CHWs will also be calculated.

### Sample size

Key underlying assumptions for this study are that there will be 20 intervention villages and 20 control villages with 50 consenting high-risk patients in each village and an estimated total of 2,000 high-risk individuals, an intra-cluster correlation coefficient (ICC) of 0.01 or 0.02
[36, 47], and two-sided alpha of 0.05. For the primary outcome, assuming the proportion of anti-hypertensive medication prescriptions in the control villages is 20% (conservative as preliminary data shows it to be <10% in the target study sites), the power to detect a 10% difference in the primary outcome of anti-hypertensive medication use is excellent (>90%) with an ICC of 0.01, and similarly high with an ICC of 0.02. Assuming a standard deviation of change in systolic blood pressure of 15 mmHg among the high-risk individuals, the power to detect a 3 mmHg net difference in this secondary outcome between the intervention and control group pre-post differences will be >90% with an ICC of 0.01 (>90% as well if ICC = 0.02).

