### Screening

Before the start of the baseline data collection, a survey will be conducted in all participating villages to screen for high-risk individuals. All village residents 40 years and above will be invited to participate in the survey, which will include a brief questionnaire on disease history and measuring blood pressure twice. All high-risk individuals screened out through this process according to the definition described above, a target minimum of 50 in each village, will be invited to participate in the study.

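### The stated power of more than 90% for a 3 mmHg systolic blood pressure difference at ICC 0.02 is modestly overstated: the plan's own inputs give about 87–89%

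*Protocol article*

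**What the plan says.** The Sample size section of the protocol article bases its power statements on "20 intervention villages and 20 control villages with 50 consenting high-risk patients in each village", giving "an estimated total of 2,000 high-risk individuals". It takes "an intra-cluster correlation coefficient (ICC) of 0.01 or 0.02" and a "two-sided alpha of 0.05".

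For systolic blood pressure, a secondary outcome, it assumes a "standard deviation of change in systolic blood pressure of 15 mmHg among the high-risk individuals" and a net difference of 3 mmHg between the arms in pre-post change. It concludes that power "will be >90% with an ICC of 0.01 (>90% as well if ICC = 0.02".

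The section mentions no allowance for loss to follow-up. The Screening section describes recruitment: all screened high-risk residents, "a target minimum of 50 in each village, will be invited to participate in the study".

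**The concern.** The power statement is a strict lower bound given at two values of the ICC. With 50 patients per village, moving from an ICC of 0.01 to 0.02 raises the design effect from 1.49 to 1.98, which cuts the effective sample size by about a quarter. One bound covering both values therefore needs checking, and all the inputs for the check are in the same paragraph.

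At stake is the accuracy of the only power figure given for a secondary outcome. The article chose its primary outcome, a process indicator, partly because treatment lowers blood pressure. The blood pressure comparison shows whether that follows, so its power should be stated correctly. A bound of more than 90% implies a type II error below 10%; the stated inputs put it at 11–13% when the ICC is 0.02.

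**Working it through.** **Inputs** (all from Sample size): k = 20 villages per arm; m = 50 patients per village, so km = 1,000 per arm; SD of change = 15 mmHg; difference = 3 mmHg; two-sided alpha = 0.05; ICC = 0.01 or 0.02.

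**Formulas**

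- Design effect: DE = 1 + (m − 1) × ICC
- Effective number per arm: n_eff = km / DE
- Standard error of the difference: SE = SD × √(2 / n_eff)
- Power, normal approximation: Φ(3/SE − 1.960)
- Power, t test: noncentral t with noncentrality 3/SE and 38 degrees of freedom (40 villages − 2)

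**Step 1. The plan's figure at ICC 0.01**

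- DE = 1 + 49 × 0.01 = 1.49
- n_eff = 1000 / 1.49 = 671.1
- SE = 15 × √(2 / 671.1) = 0.819 mmHg
- 3 / 0.819 = 3.664
- Power = Φ(3.664 − 1.960) = 95.6%; by t, 94.6%

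More than 90% is confirmed, so the standard method fits the text.

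**Step 2. The plan's figure at ICC 0.02**

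- DE = 1 + 49 × 0.02 = 1.98
- n_eff = 1000 / 1.98 = 505.1
- SE = 15 × √(2 / 505.1) = 0.944 mmHg
- 3 / 0.944 = 3.178
- Power = Φ(3.178 − 1.960) = 88.8%; by t, 87.2%

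More than 90% is not met.

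**Step 3. Does another reading of the same inputs reach 90% at ICC 0.02?**

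| Variant | Power |
|---|---|
| Normal approximation, DE = 1 + (m − 1) × ICC | 88.8% |
| DE = 1 + m × ICC = 2.00 | 88.5% |
| SD of 15 read as the within-village SD | 88.2% |
| t test, 38 df (36–37 df: 87.1–87.2%) | 87.2% |
| Normal approximation with one village fewer per arm | 87.2% |
| One-sided test | 93.7% |
| Clustering ignored (DE = 1) | 99.4% |

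Only the last two exceed 90%. The section excludes both, since it specifies a two-sided test and a non-zero ICC.

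**Step 4. How far off is it?** By the normal approximation, 90% power needs n_eff = 2 × (15 × (1.960 + 1.282) / 3)² ≈ 525 per arm. That means DE ≤ 1000 / 525.4 = 1.903, or ICC ≤ 0.903 / 49 = 0.0184.

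**Step 5. Primary outcome, for comparison.** For 20% versus 30% with the same n_eff, power is 98.9% at ICC 0.01 and 95.7% at ICC 0.02. Those statements stand.

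**Step 6. Effect of loss (illustration only).** The article gives no loss rate. If 45 of 50 per village were analysed (an assumed 10% loss), then at ICC 0.02 DE = 1 + 44 × 0.02 = 1.88, n_eff = 900 / 1.88 = 478.7 and SE = 0.970 mmHg. Power is 87.2% by the normal approximation and 85.4% by t.

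**The case against.** The strongest defence is that the gap is small and partly a matter of method. The usual design-effect formula gives 88.8%, only 1.2 points below 90%. The larger gap depends on a 38-df correction that the article does not specify. This stands as a point about severity. It does not rescue the statement, because the article gives a strict bound and not an approximate value, and both methods fall below it.

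A second defence is that the design may do better than the formula. Randomisation is stratified by country and, in China, by county and township, and the analysis accounts for this. If stratification removed an assumed 8% of the between-village variance, the normal approximation would just reach 90%. An SD of 14.7 mmHg, or 55 patients per village, would do the same. These are fair reasons not to say that the trial will lack 90% power in practice. But the Sample size section uses none of them; it states its inputs, and those inputs do not give the stated result.

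A reader might also infer three stronger criticisms, which the article does not support:

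- **That refusals lower the power further.** The calculation already counts "50 consenting high-risk patients in each village", and the Screening section's 50 is a minimum, with all high-risk residents invited. Refusal matters only in villages with too few eligible people to yield 50 who consent.
- **That power is really near 80%.** This needs consent and follow-up rates that the article does not give. A fuller protocol, not shown, may also deal with loss.
- **That a key outcome is compromised.** The article lists blood pressure among several secondary outcomes and gives it no special rank. Results will be reported with 95% confidence intervals, which show precision directly.

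**Conclusion.** Wrong as written; minor severity. At ICC 0.02 the stated inputs give power of 88.8% (normal approximation) or 87.2% (t, 38 df) for a 3 mmHg difference, 1.2 to 2.8 points below the claimed bound. The statement at ICC 0.01 is correct.

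The conclusion rests on equal villages of 50 analysed patients, the ICC applied to the change in systolic pressure, and no credit for stratification or covariate adjustment. These match what the Sample size section states, which claims no such credit. The number of villages, the number of patients and the primary outcome's power are unaffected.

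**What to change.** In Sample size, replace the parenthesis on ICC 0.02 with wording such as: about 87–89% if the ICC is 0.02, with 50 patients analysed per village. Keep the statement for ICC 0.01. If the investigators assume a loss rate, they should state it and give the power at the resulting number analysed; for illustration, an assumed 45 per village gives about 85–87% at ICC 0.02. If they wish to claim credit for stratification or a smaller SD, they should name that input and show the result.

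This is a text correction of one phrase. It needs no additional villages or patients and no change to the design or analysis; the only cost is a slightly less favourable figure.

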### Statistical analysis

All analyses will be conducted at individual level according to intention-to-treat principles, and take into account the stratification design and cluster effects. For the primary outcome, anti-hypertensive medication use, log-binomial models with random effects for villages to account for clustering and random effects for intercept to account for the pre-post correlations within individuals and a fixed effect for country to account for the stratified study design will be used. Other than the main effect from intervention and time, an interaction term between intervention and time will be added in the model to test if the slope of the pre-post changes differs by intervention or control group. To account for the heterogeneity between two countries, the two-way interaction of the country variable with intervention and time will be included into the above models. In the case of significant interaction existing, the separate analysis by country will be conducted afterward. The net effect from intervention will be reported as difference-in-difference of proportions together with model-based 95% confidence intervals obtained by transforming back from models. For continuous outcomes, such as systolic blood pressure, similar strategies will be adopted but linear models instead of log-binomial models will be used. Some adjusted analysis will also be performed to account for potential unbalanced baseline information. Other pre-specified subgroup will include analyses by sex and age (40–59 vs. 60 years or older) using similar strategy for the country variable.

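### The primary model names no village-by-time effect, so as naturally read its interval for the intervention-by-time term omits village variation in change

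*Protocol article*

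**What the plan says.** The Outcome evaluation section defines the primary outcome as the difference between arms in the pre-to-post change in the proportion treated with antihypertensive drugs. The Statistical analysis section tests this with an intervention-by-time interaction in a log-binomial model and takes the confidence interval from the model.

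The random part of that model is given as "random effects for villages to account for clustering and random effects for intercept to account for the pre-post correlations within individuals". Country enters as a fixed effect, with two-way interactions with intervention and time. For continuous outcomes, "similar strategies will be adopted but linear models instead of log-binomial models will be used". The subgroup analyses follow the same approach. The section also promises, in general terms, that the analyses will allow for stratification and clustering. It names no village-by-time effect, village random slope, cluster-robust variance or village-level analysis.

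The Sample size section assumes "20 intervention villages and 20 control villages with 50 consenting high-risk patients in each village", "an intra-cluster correlation coefficient (ICC) of 0.01 or 0.02" and "two-sided alpha of 0.05". For systolic pressure it pairs that ICC with a standard deviation of change: "Assuming a standard deviation of change in systolic blood pressure of 15 mmHg among the high-risk individuals".

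**The concern.** A random effect protects a contrast only if it contributes to the variance of that contrast. A village intercept and a person intercept each take one value for both surveys, so both vanish when baseline is subtracted from follow-up. If these are the only random effects, the interaction is judged against the scatter of about 2,000 individual changes treated as independent. The term assigned to handle clustering then does nothing for the effect being tested.

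Villages can plausibly differ in their change. Care is delivered by village health workers who are paid on performance, and control villages may have other government or project programmes. Both influences act on a whole village between the two surveys. The systolic pressure power calculation already allows for such clustering, but the analysis model as described has no parameter for it.

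At stake are the size of the primary test and the coverage of its interval. The error runs towards claiming an effect too readily. The same applies to the other pre-post outcomes and to the subgroup models.

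**Working it through.** **Inputs.** From Sample size: 20 villages per arm, 50 patients per village (1,000 per arm), ICC 0.01 or 0.02, two-sided alpha 0.05, 20% against 30% on treatment, SD of systolic change 15 mmHg, net difference 3 mmHg. From Statistical analysis: the random effects quoted above.

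**The plan's own power.** Design effect DE = 1 + 49 × ICC, which is 1.49 or 1.98. Effective n per arm = 1,000/DE = 671.1 or 505.1.
- Primary outcome, 20% against 30%: power 98.9% (ICC 0.01) and 95.7% (ICC 0.02). This agrees with "the power to detect a 10% difference in the primary outcome of anti-hypertensive medication use is excellent (>90%) with an ICC of 0.01" and with the similarly high power stated for 0.02.
- Systolic pressure: SE = 15 × √(2/671.1) = 0.819, so 3/0.819 − 1.96 = 1.70 and power is 95.6%. At ICC 0.02 the SE is 0.944 and power is 88.8%, slightly below the stated figure of more than 90%. That is a minor, separate matter.

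So the systolic pressure figures are close to a calculation that applies the ICC to change.

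**Cancellation.** Write the outcome of person i in village j at time t as fixed effects + v_j + u_ij + e_ijt. The change is fixed effects + (e_ij1 − e_ij0); v_j and u_ij are gone. With SD of change σ, the model-based variance of the difference between arms is 2σ²/1,000. If changes have ICC ρ within villages, the true variance is 2σ² × (1 + 49ρ)/1,000. The model SE is therefore 1/√DE of the true SE, and the type I error is 2 × [1 − Φ(1.96/√DE)].

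| ICC of change | DE | Model SE / true SE | Type I error | 95% CI coverage |
|---|---|---|---|---|
| 0 | 1 | 1 | 5% | 95% |
| 0.005 | 1.245 | 0.896 | 7.9% | 92.1% |
| 0.01 | 1.49 | 0.819 | 10.8% | 89.2% |
| 0.02 | 1.98 | 0.711 | 16.4% | 83.6% |

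For systolic pressure the model half-width would be 1.96 × 15 × √(2/1,000) = 1.31 mmHg. The correct half-width is 1.60 mmHg at ICC 0.01 and 1.85 mmHg at 0.02.

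**Checks under no effect.**
- Linear model, one simulated data set: a REML fit with village and person intercepts gave an interaction z of −2.7303. The unclustered comparison of individual changes also gave −2.7303. The village-level t was −2.38.
- Linear model, 5,000 runs per setting, with and without a village intercept variance: type I error 4.7–5.3% at ICC of change 0, 10.4–11.0% at 0.01 and 15.5–16.5% at 0.02.
- Binary mixed model with village and person intercepts, log link, 400 runs per setting: 4.8%, 11.8% and 16.8% at the same three values. With 400 runs the Monte Carlo standard error near 12% is √(0.12 × 0.88/400), or 1.6 points. Cancellation is only approximate here, but the inflation is much the same.
- A village-level analysis of change on the same data held 4.0–5.6%.

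These simulations had no country term, so the ICC in the table is best read as variation between villages within a country.

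**The case against.** Five points can be made for the plan.

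1. *The text does not say intercept-only for villages.* The word intercept is attached to the person-level effect, and the section opens by promising to allow for clustering. A reader might infer that the plan sets out to ignore clustering. The document does not support that. Intercept-only is the natural reading because no time-varying village term is named, but it remains a reading. What stands is that the text as written does not secure the protection it promises.

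2. *The ICC of change is explicit only for systolic pressure.* For the primary outcome the ICC is used with two proportions, without a variance of change or a within-person correlation. A reader might take 10.8% or 16.4% as the actual error rate of the primary test. The documents do not support that either. Those figures are conditional, and with no village variation in change the test holds its 5%.

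3. *The model has country interactions.* The country-by-time term lets mean change differ between China and India, so that part of the variation is absorbed. Variation between villages within a country is not.

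4. *Not every secondary outcome is affected.* The proportion receiving five or more health-worker visits is not a pre-post contrast.

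5. *An article condenses.* Degrees of freedom and covariance details may well sit in an analysis plan that is not shown. Here, though, the article does list the random effects and gives the village term the job of handling clustering. The point concerns what is stated, not what is absent.

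**Conclusion.** The concern holds in conditional form. The effect tested is the intervention-by-time interaction, and neither of the two named random effects, read as intercepts, contributes to its variance. Variation in change between villages within a country would go unmodelled, and the interval would be too narrow to the extent that such variation exists.

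If the plan's ICC of 0.01 or 0.02 applies to change in the primary outcome, the standard error is 18% or 29% too small, type I error is about 10.8% or 16.4%, and coverage is about 89% or 84%. At an ICC of change of 0.005 type I error is about 7.9%; at 0 there is no inflation. For systolic pressure the plan itself assumes 0.01 or 0.02.

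The conclusion rests on three assumptions: a village intercept only, equal villages of 50, and, for the primary outcome, an ICC of change borrowed from the systolic pressure calculation. If a village random slope was intended, the text needs only to say so.

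**What to change.** In Statistical analysis, add a village-by-time random effect to the primary model and to the models for the other pre-post outcomes and the subgroups. Base the degrees of freedom on the number of villages less arms and randomisation strata. Overall that is 40 − 2 = 38 before strata are deducted. For India alone it is 20 − 2 = 18, since randomisation there has no geographical strata. For China alone it is fewer than 18, because villages are stratified by county and township. As an alternative, use village-clustered standard errors with a small-sample correction. State that a model with village intercepts only will not be used for inference on change.

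The cost is a change of wording and somewhat wider intervals: by a factor of √1.49 = 1.22 or √1.98 = 1.41 if the ICC of change is 0.01 or 0.02. Primary power by the plan's design-effect calculation stays at about 99% or 96%, since that calculation already includes the clustering. It compares two proportions, however. For a difference in change, power also depends on the within-person correlation, which the article does not give. With 20% at baseline in both arms, the design-effect power would be 87.7% or 77.2% at a correlation of 0, and 99.3% or 96.8% at 0.5.

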### Study sites

Two counties in the Tibet autonomous region located in Southwest China – Gongbujiangda and Linzhou - and one tehsil - Ballabgarh in Faridabad District from Haryana State in northwestern India will participate in the study. Villages from these locations will be selected to take part in this study based on the site selection criteria of (1) high CVD burden, (2) limited healthcare resources, (3) having available existing CHWs or qualified candidates who can be trained to fulfill that role, and (4) local government support. A total of 40 villages will be recruited across the two countries, 20 in each country.

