### Randomization

In each country, villages will be randomized to receive the intervention or usual care. Randomization will be stratified by country. In China, all selected villages will be randomized by a 1:1 ratio to the intervention and control group with stratification by county and township (the administrative unit managing the villages). In India, randomization will not be stratified by any geographical locations. Randomization in both countries will be conducted by a study staff not involved in the intervention through a central computerized process. Group allocation will be concealed until after the baseline data collection is completed.

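### Chinese villages are randomised within county and township, but the stated model carries only country terms, so those strata go unused and a China-only analysis would contain none

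*Protocol article*

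**What the plan says.** The Randomization section sets two levels of stratification. Overall: "Randomization will be stratified by country". In China, villages are "randomized by a 1:1 ratio to the intervention and control group with stratification by county and township". India has no further level: "In India, randomization will not be stratified by any geographical locations". Study sites names two Chinese counties ("Two counties in the Tibet autonomous region located in Southwest China"). The number of townships is not given.

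The Statistical analysis section commits all analyses to "take into account the stratification design and cluster effects". For the primary log-binomial model it lists random effects for village and for individual, and then "a fixed effect for country to account for the stratified study design will be used". The treatment effect is the intervention-by-time interaction. To allow for differences between countries, "the two-way interaction of the country variable with intervention and time will be included into the above models". If an interaction is significant, each country is analysed separately. Continuous outcomes follow the same scheme with linear models. County and township are not mentioned in this section.

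**The concern.** The article does more than promise to respect the stratification: it says which term does so. That term matches the upper level of the design and omits the lower level, which applies to 20 of the 40 villages.

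The form of the term matters too. The effect of interest is a contrast of changes. In a linear model a stratum main effect shifts both surveys equally and drops out of that contrast. To gain from stratification, the model needs stratum-by-time terms (or stratum effects on follow-up given baseline). On the plain reading country has such a term. County and township have none.

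At stake is the precision that stratifying in China was meant to give. Stratification balances townships across arms, which lowers the true variance of the effect estimate. If the model ignores townships, their differences in change stay in the error term and the reported interval is wider than the design warrants. The China-only analysis is the most exposed: country and its interactions vanish there, and only 20 villages remain.

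**Working it through.** **1. The plan's own power figure.** Inputs from Sample size: 20 villages of 50 per arm, ICC 0.01 or 0.02, 20% against 30%, two-sided 0.05. Design effect = 1 + 49 × ICC = 1.49 or 1.98. Effective n per arm = 1000/1.49 = 671 or 1000/1.98 = 505. Power = Φ{[0.10 − 1.96√(2 × 0.25 × 0.75/n)] / √((0.16 + 0.21)/n)} = 98.9% or 95.7%. The stated power of over 90%, and similarly high at ICC 0.02, is reproduced.

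**2. Design against model.**

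| Level | In the randomisation | In the stated model |
|---|---|---|
| Country | yes | main effect, and interactions with intervention and time |
| County (China) | yes | no |
| Township (China) | yes | no |
| Area within India | no | not needed |

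**3. Which country term does the work.** In a linear example with arms deliberately unbalanced by country, the intervention-by-time estimate is 0.4394 with no country term, 0.4394 with a country main effect, and 0.5662 once country by intervention and country by time are added. The interactions, not the main effect, bring the country stratum into the effect estimate.

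**4. Cost of omitting township.** This step works with village-level mean changes, so it presumes that village variation in change is modelled. Assumptions, none of them from the protocol: 5 townships of 4 villages in China, pre-post correlation 0.5, village SD of change 5 points, country difference in change 10 points.

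- Sampling variance of a village's change: 2 × 0.2 × 0.8 × (1 − 0.5)/50 = 0.0032. Adding village variance 0.05² = 0.0025 gives 0.0057.
- True standard error, 20 against 20 villages: √(0.0057 × (1/20 + 1/20)) = 0.0239.
- Without a township term, the expected township sum of squares, 4 × (5 − 1) × s², falls into the residual. The pooled model with country by time has 40 − 3 = 37 residual df.
- s = 5 points: 16 × 0.0025/37 = 0.00108, and √((0.0057 + 0.00108)/0.0057) = 1.09.
- s = 10 points: 16 × 0.01/37 = 0.00432, and √((0.0057 + 0.00432)/0.0057) = 1.33.

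A null simulation (8,000 runs, randomisation within strata, nominal 5%) agrees:

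| Township SD of change | Mean SE, country by time only | Mean SE, township by time | Type I error, country only | Type I error, township |
|---|---|---|---|---|
| 5 points | 0.0258 | 0.0237 | 3.4% | 4.9% |
| 10 points | 0.0312 | 0.0237 | 1.6% | 4.9% |

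The ratios are 0.0258/0.0237 = 1.09 and, from unrounded values, 0.03116/0.02365 = 1.32. The true SD of the estimate is 0.0239 in every case. With no country or township differences in change, type I error is 5.0% with country and 4.9% with township terms.

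**5. Range over the number of townships.** With k equal townships the sum of squares is (20/k)(k − 1)s². For k = 4 to 10 the pooled ratio runs from 1.08 to 1.10 at 5 points and from 1.31 to 1.36 at 10 points. The result depends far more on how much townships differ than on how many there are.

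**6. China-only model.** Residual df are 20 − 2 = 18. At k = 5: 0.04/18 = 0.00222 gives √(0.00792/0.0057) = 1.18, and 0.16/18 = 0.00889 gives √(0.01459/0.0057) = 1.60.

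**7. The same omission in the model as literally written.** The listed random effects are intercepts for village and individual, with no village-by-time term. In the linear, balanced case the standard error then rests on person-level change, with variance about 0.16 + 0.0025 = 0.1625 over 2,000 people. Township adds 16 × 0.0025 × 50/1997 = 0.0010 (0.6%) at 5 points, or 0.0040 (2.5%) at 10 points, so the standard error changes by about 0.3% or 1.2%.

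**The case against.** The strongest reply has four parts.

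*The article is condensed.* How townships are coded is normally left to the full plan, and the general sentence already commits to the stratification design. This carries some weight. But the article goes on to name the term that does the accounting, and that term does not match its own randomisation section.

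*The harm depends on a term the plan does not contain.* This stands. Without village-by-time variation in the model, leaving out township hardly moves the standard error (step 7). Whether that variation should be modelled is a separate question; the 9% and 32% apply only if it is.

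*Validity is not threatened.* This also stands. The estimate is unbiased, the test errs on the conservative side, and the planned primary power has room to spare.

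*Township terms may cost more than they return.* This stands in part. With 10 townships of 2 villages, fixed township terms would leave the China-only model 20 − 11 = 9 residual df.

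A reader might go further and infer that, because a country main effect cancels out of a pre-post contrast, the stratified design is not used at all. The documents do not support that. Country interactions with intervention and time are in the model. That sentence could be read as one three-way term, but the plain reading includes country by time, which does not cancel. India has no other strata to use. Exact cancellation is also a linear-scale result. The primary effect is a log-binomial estimate transformed back to proportions, where the baseline level matters: with a time ratio of 1.2 and an interaction ratio of 1.5, the difference-in-difference is 0.05 × 1.2 × 0.5 = 3 points at a 5% baseline and 0.20 × 1.2 × 0.5 = 12 points at 20%.

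**Conclusion.** The point holds in a limited form. The randomisation has county and township strata in China, the stated model does not, and a separate Chinese analysis would have no stratum left. The two sections should be brought into line.

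The consequence is a possible loss of precision and a conservative test, without bias. It arises only if townships differ in pre-post change and village-level variation in change is modelled. Under the assumptions in step 4 the pooled standard error is then about 9% too large at a township SD of 5 points and about 32% at 10 points, and more in a China-only model. These sizes are illustrations, because the protocol gives neither the number of townships nor any variance component for change.

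A reader might also try to turn the planning ICC into a fixed variance saving, since the between-village share of a village mean's variance is 50 × 0.01/1.49 = 34% or 50 × 0.02/1.98 = 51%. The documents do not support that step: they do not say what share of that variation townships explain, nor that the ICC applies to change.

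**What to change.** In Statistical analysis, keep the country terms and add the actual Chinese randomisation strata as stratum-by-time terms, in both the pooled and the China-only models, with India as a single stratum. Main effects for county and township alone would not be enough, since in the linear models they drop out of the pre-post contrast. If townships are many or small, keep county by time as a fixed effect and make township by time random. State the number of townships and the number of villages in each, so that this choice can be made before the data are analysed.

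The cost is wording and a few village-level degrees of freedom in China. With 5 townships as fixed terms, residual df fall from 37 to 33 in the pooled model (t quantile 2.03 in both cases) and from 18 to 14 in the China-only model (2.10 to 2.14). No new data are needed.
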